## Abstract

**Objectives:**

In this study, we will investigate the effect of hydroxychloroquine on the prevention of novel coronavirus disease (COVID-19) in cancer patients being treated.

**Trial design:**

This is a two-arm, parallel-group, triple-blind, phase 2–3 randomized controlled trial.

**Participants:**

All patients over the age of 15 years from 5 types of cancer will be included in the study. Patients with acute lymphoid and myeloid leukemias in the first line treated with curative intent, patients with high-grade non-Hodgkin’s lymphoma treated with leukemia regimens, and patients with non-metastatic breast and colon cancer in the first line of treatment will enter the study.

**Intervention and comparator:**

Patients are randomly assigned to two groups: one being given hydroxychloroquine and the other is given placebo. During 2 months of treatment, the two groups will be treated with hydroxychloroquine every other day with a single 200-mg tablet (Amin® Pharmaceutical Company, Isfahan, Iran) or placebo (identical in terms of shape, color, and smell). Patients will be monitored for COVID-19 symptoms during follow-up period.

If any COVID-19-related signs or symptoms occur, they will be examined, thoroughly, investigated with a high resolution computerize tomography (CT) scan of the lungs and nasopharyngeal swab assessed by RT-PCR for SARS-CoV-2 virus. This study will be performed in five centers affiliated to Mashhad University of Medical Sciences, Mashhad, Iran.

**Main outcomes:**

The primary end point of this study is to investigate the incidence of COVID-19 in patients being treated for their cancer and receiving prophylactic Hydroxychloroquine.

**Randomization:**

Randomization will be performed using random permuted blocks. By using online website (www.randomization.com), the randomization sequence will be produced by quadruple blocks. The allocation ratio in intervention and control groups is 1:1.

**Blinding (masking):**

Participants and caregivers do not know whether the patient is in the intervention or the control group. Those assessing the outcomes and data analyzer are also blinded to group assignment.

**Sample size:**

The calculated total sample size is 60 patients, with 30 patients in each group.

**Supplementary Information:**

The online version contains supplementary material available at 10.1186/s13063-021-05292-8.

## Introduction

### Background and rationale {6a}

The emergence of coronavirus disease 2019 (COVID-19) caused by a novel virus from the coronavirus family named SARS-CoV-2 has imposed enormous health and economic problems worldwide.

On the last days of 2019, this disease was reported for the first time in Wuhan, capital of Hubei province, in China, presented with pneumonia. Due to the rapid dissemination of the disease that leads to a pandemic in less than 3 months, there are great concerns about health systems in most countries.

The unknown nature of the virus and the effective methods of prevention and treatment, as well as the high speed of infection spread challenged the scientists. Most of the studies have shown higher incidence and more severity of COVID-19 among cancerous patients [1–7].

COVID-19 imposes great concerns on the patients and their health care providers. The horror of COVID-19 disease that could cause significant morbidity and mortality in immunocompromised patients and lack of specific treatment till now interfere with cancer treatment [8]. Most studies have shown that COVID-19 disease is more severe in cancer patients than others, and the people with cancer have a higher risk of death from COVID-19 disease [6, 9–16].

Some of the most reliable cancer centers in the world have recommended guidelines and advisories for cancer treatment in the COVID-19 era. Most of them have ended up with delay in specific treatment or administration of less toxic regimens. Unfortunately, the consequences of delaying cancer treatment will be determined in the future. Taking rational therapeutic strategies into consideration is of great importance. All cancers must be treated with proper and timely modalities.

As it seems, COVID-19 and its complications are not going to end soon and even it might be a permanent guest of the human being. Nowadays, most of the medical facilities and health care workers capacity are being used by the COVD-19 crisis. Therefore, all of the main health indices such as morbidity and mortality of cancer are being negatively affected.

Several studies have shown the antiviral effect of hydroxychloroquine [17–20]. Hydroxychloroquine (HCQ) is easily available, is easy to take in the form of an oral tablet, and has few monitorable side effects. The drug has no known interaction with chemotherapeutic agents, according to UpToDate®, an evidence-based physician-authored clinical decision support resource and Lexicomp® Drug Interactions [21].

It has been shown that hydroxychloroquine has an inhibitory effect on various viral infections such as adenovirus, influenzas’ virus, and HIV-1. This effect is exerted by preventing the virus from cell entry. Hydroxychloroquine also has good effects on intracellular organisms like malaria and even Coxiella Burnetti. In other studies, in vitro and in vivo antiviral effects of the drug have been shown on the coronavirus family including SARS-CoV-2 [19, 22–26].

### Objectives {7}

Although performing all current approved preventive protocols such as social distancing, hand washing and disinfection, and wearing a face mask in patients have had relatively desirable results, they are not enough to prevent COVID-19 in such susceptible patients.

In this study, we aimed to investigate the effect of the drug hydroxychloroquine on reducing the incidence of COVID-19 disease in cancer patients being treated for their cancer. On the other hand, we decided to compare the rate of COVID-19 infection, the severity of the disease, and its complications in the two groups of cancer patients receiving hydroxychloroquine or placebo.

### Additional consent provisions for collection and use of participant data and biological specimens {26b}

This trial does not involve collecting biological specimens for storage.

### Trial design {8}

This is a phase II–III multicenter two-arm randomized clinical trial designed for cancer patients who have to continue their cancer-specific treatment during COVID-19 pandemic. This trial designed to compare hydroxychloroquine with placebo in COVID-19 disease prevention. The patient allocation ratio is 1:1.

## Methods: participants, interventions, and outcomes

### Study setting {9}

This trial will be performed in two tertiary hospitals, Ghaem and Imam Reza, and three oncology clinics in Mashhad. Referred cancer patients are classified into low-, moderate-, and high-risk groups for COVID-19 involvement. Taking into account statistical considerations, we decided to select the patients just from low- and high-risk groups.

In the low-risk cancers, patients with the most common cancers, breast and colon, were selected. Among the high-risk cancers, patients with acute lymphoblastic or myeloid leukemia and those who have high-grade non-Hodgkin lymphomas treated with leukemia like regimens were selected. These patients would be included if they have below eligibility criteria.

### Eligibility criteria {10}

All patients must have these inclusion criteria:
Hematologic malignancies (AML, ALL, high-grade NHL) should be in the first line of treatment with the intention to cure.Included solid tumors should be non-metastatic.Patients older than 15 years

All patients must *not* have bellow criteria:
Allergy to hydroxychloroquineBody weight below 35 kgHistory of retinopathyHistory of cardiac diseasePresence of any sign or symptom of COVID-19 before trial entryPositive serologic screening for SARS-CoV-2 antibodiesCOVID-19 infection during the first two weeks of trial entry (these patients would be excluded from the study, considering the maximum incubation period of 2 weeks for the infection)Diabetes mellitusDiseases causing immunodeficiency other than cancerChronic pulmonary diseaseImmunosuppressive drugs other than cancer chemotherapeutic agents

### Who takes informed consent? {26a}

Eligible patients are selected by the treating physician and given general information about the study. Then, for more familiarity and possible questions and answers, they are referred to the researchers in the clinic. There, after a more detailed introduction of the study in plain language, the informed consent is signed by the patient or his/her legal guardian.

### Intervention {11}

#### Intervention description {11a}

Patients in both study arms will receive a new drug in addition to their anti-cancer treatment. They will receive hydroxychloroquine in the intervention arm, and in the control arm, they will receive placebo. Hydroxychloroquine is administered as one 200-mg tablet every other day. Reasons for using this dose are HCQ long half-life, unknown metabolism, gastrointestinal intolerance in patients undergoing chemotherapy, and minimizing potential side effects while maintaining the efficacy. Participants will take the drug or placebo for 2 months.

Cancer-specific therapies will be chosen according to valid oncologic guidelines by treating oncologist as well as the patient’s opinion. Researchers do not have any role in regimen selection.

Patients are monitored for symptoms and signs of COVID-19 for 10 weeks, including 8 weeks of study intervention and 2 weeks after completion of medication. The symptoms of COVID-19 disease, fever, shortness of breath, cough, myalgia, abdominal pain, and diarrhea, are taught to patients, and if any suspicious symptom occurs, the patient goes to the dedicated clinic. Treating physicians, also, refer the patient to the dedicated clinic whenever they experience suspicious COVID-19 symptoms or any symptoms that are not attributable to the patient’s underlying cancer and its treatment.

Referred patients will be visited by an internal medicine specialist, at a dedicated clinic. For all of these patients, more paraclinical investigations (Additional file 1) are performed.

Based on the symptoms and the result of polymerase chain reaction (PCR) test, the conditions are as follows:
If a patient has a positive PCR test and he/she has symptoms of COVID-19, he/she is considered to have COVID-19.If in a patient the PCR test for 3 consecutive times, each 24–48 h apart, is negative and the patient has typical COVID-19 symptoms, he/she is considered to have COVID-19.A patient with 3 negative PCR tests, whose symptoms are not completely typical and have a justifiable cause and disappears in a few days or with specific treatments for other infectious causes, is not considered to have COVID-19.It should be noted that asymptomatic patients are not evaluated by PCR.

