### Criteria for discontinuing or modifying allocated intervention {11b}

During the study, patients will be monitored for cardiac complications by performing an electrocardiogram (ECG) in the first visit and each chemotherapy session or at least once, every 4 weeks. The most important point in ECG is to calculate corrected QT interval; if the interval is longer than 500 ms, the drug will be discontinued, a drug complication is recorded, and the patient referred to a cardiologist.

At the beginning of the study, a comprehensive history of ophthalmologic problems will be obtained. All patients will be evaluated for any new visual disturbances during the study. In case of new visual disturbances, an examination by an ophthalmologist is warranted and a drug complication is recorded. Since the ocular side effects of HCQ have been reported in long-term use, often after 12 months, periodic examination in asymptomatic patients was not considered.

All patients with hydroxychloroquine drug side effects were excluded from the study in addition to the necessary treatment and compensation measures.

There is not any evidence-based recommendation for baseline cardiac function assessment and ophthalmologic examination in short-term and low dose use of hydroxychloroquine.

Other less common side effects such as hematologic, skin, and gastrointestinal complications are monitored by treating physician. Besides, an Internist is introduced to patients by researcher team just to answer the patients concerns about the study medication or to make an out-of-schedule visit if needed.

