#### Conditions for unblinding {17b}

Whenever a patient experiences any attributable drug side effects, her/his information will be recorded, the intervention would be stopped and necessary care will be applied. Then his/her study group will be revealed to the treating physician.

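### An ambiguous gut episode can become either a primary COVID-19 event or a side-effect removal, with no rule to decide which; if hydroxychloroquine causes excess gut symptoms, this happens more often in the active arm

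*Protocol article*

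**What the plan says.** All references are to the protocol article.

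- **Symptoms.** Intervention description {11a}: "The symptoms of COVID-19 disease, fever, shortness of breath, cough, myalgia, abdominal pain, and diarrhea, are taught to patients". Any suspicious symptom sends the patient to the dedicated clinic. Treating physicians also refer "any symptoms that are not attributable to the patient’s underlying cancer and its treatment"; effects of the study drug are not set apart.
- **PCR-negative case rule.** {11a}, second rule: if PCR, done three times in a row, "is negative and the patient has typical COVID-19 symptoms, he/she is considered to have COVID-19". Typical is not defined.
- **Non-case rule.** {11a}, third rule: a patient with three negative PCR tests "whose symptoms are not completely typical and have a justifiable cause and disappears in a few days", or with treatment for another infection, is not a case.
- **Side effects.** Section {11b}: "Other less common side effects such as hematologic, skin, and gastrointestinal complications are monitored by treating physician". Section {11a} gives "gastrointestinal intolerance in patients undergoing chemotherapy" among the reasons for the dose.
- **Consequence of a side effect.** Section {11b}: "All patients with hydroxychloroquine drug side effects were excluded from the study". Section {17b}: "Whenever a patient experiences any attributable drug side effects, her/his information will be recorded, the intervention would be stopped", after which the treating physician learns the group.
- **Data and analysis.** Section {18b} collects no outcome data once a participant discontinues or deviates. Section {20c} makes the analysis per-protocol, leaves dropouts out and imputes nothing.
- **Who decides.** Section {5d} gives the clinic physician both the evaluation of COVID-19 and the management of possible side effects.

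**The concern.** The two labels have opposite consequences for the primary endpoint. Called COVID-19, a gut episode adds one to the numerator. Called a drug side effect, it takes the patient out of numerator and denominator, and nothing later is recorded. Nothing in the article says which question is settled first, or on what criterion a gut symptom is assigned to COVID-19, the study drug or chemotherapy.

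Blinding prevents knowledge of the arm from steering the label. It does not equalise the number of episodes that need one. If hydroxychloroquine causes gut symptoms beyond those of chemotherapy, more active-arm patients meet the ambiguous rule. The primary result would then partly reflect tolerability, in a comparison expected to contain very few cases.

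**Working it through.** **1. Can the error differ by arm under blinding?** Let *b* be the chance of an ambiguous gut episode from chemotherapy or other causes (both arms), *e* the excess caused by the drug (active arm only), *s* the chance that such an episode is scored as a case, and *r* the chance that it is labelled a side effect. Blinding makes *s* and *r* equal between arms.

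- Placebo: false cases *b·s*, removals *b·r*.
- Active: false cases *(b + e)·s*, removals *(b + e)·r*.
- Difference: *e·s* and *e·r*.

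Both arms are affected whenever *b* > 0. The arms differ whenever *e* > 0 and the label is used at all. The documents give none of these four quantities.

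**2. Does {11a} already close the false-case route?** Only in part. The third rule needs symptoms that are not fully typical, a justifiable cause, and resolution within days or with treatment for another infection. It does not name the study drug as a cause, and a gut effect lasting as long as dosing would not meet the resolution condition. It keeps *s* low but does not set it to zero, and it has no bearing on *r*.

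**3. How much does one patient weigh?** Inputs from section {14}: incidence 1% to 8%, decrease of about 40% (read as relative), 30 per group. I take the 30 as stated. It is not reproduced by the two-proportion formula (918 per arm at 8%, 7,785 at 1%, two-sided), but that is a separate matter and this point does not depend on it.

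- At 8%: control 30 × 0.08 = 2.4 cases; active 30 × 0.08 × 0.6 = 30 × 0.048 = 1.44 cases; difference 8.0 − 4.8 = 3.2 points.
- At 1%: 30 × 0.01 = 0.3 and 30 × 0.006 = 0.18 cases; difference 0.4 points.
- One patient: 1/30 = 3.3 points.

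One reclassified patient exceeds the assumed difference even at the most favourable incidence.

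**4. Illustration of false cases (assumed rates, not from the documents).** Let *f* = *e·s* be the excess false-case rate in the active arm. With control 8% and true active risk 4.8%, apparent active risk = 1 − (1 − 0.048)(1 − *f*).

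| *f* | Apparent active risk | Apparent risk ratio |
|---|---|---|
| 0 | 4.8% | 0.60 |
| 2% | 6.7% | 0.84 |
| 5% | 9.56% | 1.20 |
| 10% | 14.3% | 1.79 |

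The range includes zero because the drug may cause no excess, or no such episode may be scored as a case.

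**5. Illustration of removal (assumed rates).** Take no true effect, 8% in both arms. If blinded labelling removes 25% of true cases in *each* arm, with 10% of non-cases removed on active drug and 5% on placebo:

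- Active: 0.08 × 0.75 / (0.08 × 0.75 + 0.92 × 0.90) = 0.060/0.888 = 6.76%.
- Placebo: 0.060 / (0.060 + 0.92 × 0.95) = 0.060/0.934 = 6.42%.
- Ratio: 6.76/6.42 = 1.05.

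If instead the same removal (25% of cases, 5% of non-cases) occurred in the active arm only, the ratio would be 6.42/8 = 0.80. That larger distortion needs true cases to be removed preferentially on active drug, for which the article gives no mechanism.

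**The case against.** The strongest case against rests on five observations.

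- **The third rule of {11a} is a real safeguard.** A resolving gut upset with an evident cause and three negative PCR tests would often be a non-case. The symptom list is what patients are taught so that they attend; no text says that isolated diarrhoea or abdominal pain is typical. This stands as a limit on false cases, but typical is undefined and removal is untouched.
- **The overlap is partly inferred.** Section {11b} names the gastrointestinal class and calls it less common. The Limitations name nausea and vomiting, neither of which is on the COVID-19 list. Section {22} names QT prolongation, arrhythmia and retinopathy. A reader might infer that the article lists diarrhoea and abdominal pain as drug effects; it does not. That they fall within the class is a reasonable inference only.
- **The exclusion sentence follows the cardiac and ocular text.** It nevertheless covers all patients with side effects, and {17b} applies to any attributable side effect.
- **A reader might infer that only the active arm is affected.** The documents do not support this. Labels are given blind, the group is revealed after the intervention stops, and placebo patients also have chemotherapy gut symptoms.
- **A reader might infer that the rule manufactures a benefit by deleting true active-arm cases.** A true COVID-19 episode looks alike in both arms to a blinded assessor, so deletion at similar rates largely cancels (step 5).

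It is also fair that one patient outweighing the assumed effect follows from 30 per arm and would hold for any single error. It shows how little misclassification the comparison tolerates, not how often this error occurs.

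**Conclusion.** The point holds in a limited form. Sections {11a} and {11b} give the same kind of episode two labels with opposite consequences for the primary endpoint, and {17b}, {18b} and {20c} turn the side-effect label into loss from the analysis. No order or criterion is fixed. If the drug causes excess gut symptoms, both errors occur more often, though not exclusively, in the active arm, and blinding does not prevent this.

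The size and net direction of the bias cannot be computed, because no gut side-effect rate or labelling rate is given; the risk ratios above are illustrations under assumed rates. What the plan's own figures do show is the lack of margin: at most 2.4 versus 1.44 expected cases, with one patient worth 3.3 points against an assumed difference of 3.2. This rests on reading the 40% as a relative decrease and on the top of the stated incidence range.

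**What to change.** Reconcile {11a}, {11b}, {17b}, {18b} and {20c} for endpoint scoring. Clinical handling of side effects is a separate matter and is not addressed here.

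1. Score every symptomatic episode against the case definition, blinded to arm and before any side-effect label is applied.
2. Define typical so that gut-only symptoms do not qualify under the PCR-negative rule. Alternatively, keep the rule and add a sensitivity analysis restricted to PCR-positive cases.
3. Record side effects as a separate variable that does not remove the patient from the numerator or denominator of the primary analysis.
4. Report by arm the number of gut-only episodes and of patients removed for side effects, including those whose later outcomes were not collected.

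The cost is a few sentences of endpoint wording and a blinded re-scoring of recorded episodes; recruitment is already over (Trial status). There are two downsides. A true PCR-negative, gut-only case would be missed. Outcomes not collected after discontinuation cannot be recovered, so for those patients the report can only show how many there were in each arm and how far the result could move.

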### Explanation for the choice of comparator {6b}

In the control group, in addition to receiving specific cancer treatment, they are given placebo. All patients use standard preventive health measures including hand hygiene, social distancing, face mask, and isolation.

### Criteria for discontinuing or modifying allocated intervention {11b}

During the study, patients will be monitored for cardiac complications by performing an electrocardiogram (ECG) in the first visit and each chemotherapy session or at least once, every 4 weeks. The most important point in ECG is to calculate corrected QT interval; if the interval is longer than 500 ms, the drug will be discontinued, a drug complication is recorded, and the patient referred to a cardiologist.

At the beginning of the study, a comprehensive history of ophthalmologic problems will be obtained. All patients will be evaluated for any new visual disturbances during the study. In case of new visual disturbances, an examination by an ophthalmologist is warranted and a drug complication is recorded. Since the ocular side effects of HCQ have been reported in long-term use, often after 12 months, periodic examination in asymptomatic patients was not considered.

All patients with hydroxychloroquine drug side effects were excluded from the study in addition to the necessary treatment and compensation measures.

There is not any evidence-based recommendation for baseline cardiac function assessment and ophthalmologic examination in short-term and low dose use of hydroxychloroquine.

Other less common side effects such as hematologic, skin, and gastrointestinal complications are monitored by treating physician. Besides, an Internist is introduced to patients by researcher team just to answer the patients concerns about the study medication or to make an out-of-schedule visit if needed.

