#### Methods of analyses to handle protocol non-adherence and statistical methods to handle missing data {20c}

The analysis is based on per-protocol and any dropout or group crossing will be excluded from the final analysis. The probable missing data will not be imputed.

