#### Adverse event reporting and harms {22}

In the occurrence of any of the known side effects of the drug, including prolongation of the QT interval and arrhythmia and ocular complication, retinopathy, the information obtained by the treating physician will be reported. This information is recorded by the DMC and if the drug complication is confirmed, the patient will undergo the necessary treatment measures.

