## Discussion

This randomized clinical trial is designed to investigate the effect of HCQ on the prevention of COVID-19 in cancer patients. Safety and performance are also monitored.

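### Removing patients with side effects from the study after randomisation can bias the COVID-19 comparison and cuts safety information off at the first complication

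*Protocol article*

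**What the plan says.** The handling of a patient with a side effect is spread over several sections of the protocol article.

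- **{11b}, discontinuation criteria.** For a QTc above 500 ms, "the drug will be discontinued, a drug complication is recorded, and the patient referred to a cardiologist". For new visual disturbance, "an examination by an ophthalmologist is warranted and a drug complication is recorded". Then, for side effects in general: "All patients with hydroxychloroquine drug side effects were excluded from the study". For other organ systems: "Other less common side effects such as hematologic, skin, and gastrointestinal complications are monitored by treating physician".
- **{17b}, unblinding.** "Whenever a patient experiences any attributable drug side effects, her/his information will be recorded, the intervention would be stopped"; care follows, and only then is the group disclosed to the treating physician.
- **{18b}, retention.** Outcome data are not collected on participants who discontinue or deviate from the intervention.
- **{20c}, non-adherence and missing data.** The analysis is per-protocol, "any dropout or group crossing will be excluded from the final analysis", and nothing is imputed.
- **{22}, harms.** Reporting begins "In the occurrence of any of the known side effects of the drug", with QT prolongation, arrhythmia and retinopathy as the named examples. The data monitoring committee records the information.
- **{12}, outcomes.** COVID-19 incidence is primary and severity is secondary, both assessed over the 8 weeks of treatment and up to 2 weeks afterwards.
- **Discussion.** "Safety and performance are also monitored". No safety endpoint is defined.

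**The concern.** A side effect of the study drug arises after randomisation and may be caused by the allocation. If it removes the patient from the study, the patients who remain are no longer the groups that randomisation created. The protection it gives to the COVID-19 comparison is weakened to an extent that cannot be estimated, because the removed patients' outcomes are not collected.

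The same chain affects harms. Patients who had a complication are not observed further, and they do not belong to the only analysis population the article names. What reaches the record also depends on someone attributing the event to the drug. In patients on chemotherapy, cytopenia, infection or vomiting usually has another plausible explanation. A placebo arm allows such events to be compared without case-by-case attribution, but the reporting rules as written do not use that advantage.

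**Working it through.** The article gives no side-effect rate and no safety calculation, so there is no figure to reproduce. The check sets the sections side by side and then illustrates the size with assumed counts.

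**1. Does a side effect end treatment or end participation?** {17b} says the intervention stops. {11b} treats stopping the drug as one step (the QTc rule) and removal from the study as another, applied to all patients with side effects. {18b} stops outcome collection once treatment is discontinued. {12} has patients assessed for the whole 8 + 2 = 10 weeks. These do not agree. Under {11b} and {18b} together, COVID-19 status after the side effect is unknown.

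**2. Are these patients in any analysis?** {20c} names one set, per-protocol without dropouts. A patient removed under {11b} is not in it.

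**3. Is the complication itself lost?** No. {11b} records QTc and visual complications, {17b} records any attributable side effect before the intervention stops, and {22} has the committee record it. ECGs are planned at the first visit and at each chemotherapy session, or at least every 4 weeks, without distinction by arm. First complications and QTc values up to that point should therefore exist for both arms.

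**4. Which events have a route to the record?** {22} is worded around known effects. {17b} is wider but requires attribution. {11b} has haematologic, skin and gastrointestinal effects monitored, with no recording step stated there. An event not attributed to the drug has no stated reporting route.

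**5. Illustration for safety.** Inputs: 30 per arm ({14}); side-effect counts assumed; Fisher's exact test, two-sided.

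| Assumed side effects, HCQ v placebo | All randomised | p | Per-protocol set after exclusion |
|---|---|---|---|
| 6 v 0 | 6/30 v 0/30 | 0.024 | 0/24 v 0/30 |
| 6 v 1 | 6/30 v 1/30 | 0.10 | 0/24 v 0/29 |

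For the first row, p = 2 × C(30,6)/C(60,6) = 2 × 593,775/50,063,860 = 0.024.

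For one arm: 5/30 is 17% (exact 95% CI 5.6% to 34.7%). After exclusion it reads 0/25, with two-sided upper limit 1 − 0.025^(1/25) = 13.7%.

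**6. Illustration for efficacy.** {14} cites an incidence of 1 to 8% and assumes a decrease of about 40%, read here as relative. Assume the cited incidence applies over the 10 weeks.

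- At 8%: 30 × 0.08 = 2.4 expected cases on placebo and 30 × 0.048 = 1.44 on HCQ, a difference of 0.96.
- At 1%: 30 × 0.01 = 0.3 and 30 × 0.006 = 0.18, a difference of 0.12.

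One case missed because the patient had been removed for a side effect is thus at least as large as the whole expected difference. The direction of the bias cannot be determined from the document.

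**The case against.** The strongest reply is that the events are kept. {11b}, {17b} and {22} all call for the complication to be recorded, {18b} stops outcome data (which {12} defines as COVID-19 incidence and severity), and {20c} follows a section on primary and secondary outcomes. Nothing says that recorded complications are deleted or that safety is to be analysed per protocol. This stands. A reader might infer that the safety comparison is empty by construction; the document does not support that. It is empty only if safety is analysed in the one set that {20c} names.

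Two other stronger readings also fail.

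- A reader might infer that only known hydroxychloroquine effects are captured. {17b} covers any attributable side effect, and {11b} has haematologic, skin and gastrointestinal effects monitored. The gap is limited to events not attributed to the drug.
- A reader might infer that exclusion acts in the hydroxychloroquine arm only, because a placebo patient cannot have a hydroxychloroquine side effect once the group is known. In {17b} the event is recorded and the intervention stopped before disclosure, so attribution is made blind in both arms. No section reclassifies or reinstates a placebo patient.

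It is also fair to say that safety is not an endpoint, and that a safety set with tables may properly be left to a fuller document. The point does not rest on their absence. It rests on rules the article does state: removal from the study, no further outcome data, and a single per-protocol analysis.

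**Conclusion.** The point holds in this form. As written, the plan removes patients after randomisation for a treatment-related reason, stops collecting their outcomes and leaves them out of its only analysis. That can bias the COVID-19 comparison, and with few cases expected a single lost case is as large as the assumed effect or larger. Safety is truncated at the first side effect and ascertained by attribution, and it would vanish from the analysed set if that set were used for harms.

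The rules are clear from the text; the size of their effect is not. The side-effect counts are assumptions, since the document gives no rate. The 0/24 and 0/25 results further assume that recorded events are not counted outside the per-protocol set. The efficacy figures assume that the cited incidence applies over 10 weeks and that the 40% decrease is relative.

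**What to change.** Reconcile {11b}, {17b}, {18b}, {20c} and {22} so that stopping the study tablets does not mean leaving the study.

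1. **Follow-up.** Keep patients who stop because of a side effect in COVID-19 follow-up to week 10.
2. **Efficacy analysis.** Analyse COVID-19 incidence in the groups as randomised, including these patients. Present the per-protocol analysis as a sensitivity analysis.
3. **Safety analysis.** Tabulate all recorded adverse events and QTc values by arm, with exact 95% confidence intervals, over all randomised patients who took at least one tablet, regardless of attribution.
4. **Reporting.** Word {22} so that events not attributed to the drug also have a route to the record. Report every exclusion by arm with its reason.

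The scope is limited by timing. {15} puts the end of recruitment in January 2021. Ten weeks from 31 January is 11 April 2021, and the trial status is dated 26 March 2021, so follow-up was nearly or fully complete. The changes therefore apply to data already recorded or still retrievable from clinic, ECG and hospital records, and outcomes that cannot be recovered should be declared as missing.

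The cost is revised wording, one more set of tables, some record retrieval and possibly some missing outcomes. No change to the clinical handling of side effects is proposed.
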